#### Analysis of Data

Difference-in-difference analyses will be used to address any differences in sickness absence, health care refunds, and health-related quality of life between the trial arms at the unit level. Cost-effectiveness and cost-benefit analyses will compare the trial arms in terms of incremental costs based on direct and indirect costs related to interventions throughout the intervention period.

At the individual level, outcomes will be analyzed based on changes from enrollment. Moreover, 2-tailed *t* tests or Mann-Whitney *U* tests and chi-square tests will be used when appropriate. A generalized linear mixed effects Poisson model will be used to investigate possible differences in percentage of sick leave between the 2 trial arms. A multivariable, multilevel logistic, ordered logistic, and linear regression allowing for clustering at the unit level will be used according to the outcome measure (OM) analyzed. To consider changes owing to the pandemic-related temporary halt of the study, other statistical methods such as stratification will be relevant.

We will use 2-sided *P* values with *α*<.05 level of significance for all tests.

The analysis will be according to ITT regardless of protocol adherence.

Results will be reported in line with CONSORT (Consolidated Standards of Reporting Trials) guidelines.

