### Evaluation Outcomes

The *Health in work* program and the Inclusive Work Agreement have several complex, nongraded aims, which focus on improved work environment, sustainable job participation, and prevention and reduction of sickness absence. The *Health in work* program especially pinpoints work participation as an aspect that contributes to better health. However, it is not known to what extent the systematic intersectoral collaboration between NAV and specialist health services in HIW interventions is an effective use of resources. Therefore, it is impossible to define a single primary OM for this trial and, thus, the four primary OMs are as follows: (1) change in overall sickness absence rates (self- and physician-certified) at the workplace (unit level) in percentage of planned workdays for the period 24 months before allocation compared with the period 12-24 months after allocation (OM 1); (2) change in health care use, assessed using data from the National Register of Control and Health Service Refunds (The Norwegian Directorate of Health) and the Norwegian Patient Register (The Norwegian Directorate of Health), for the period 24 months before allocation compared with the period 12-24 months after allocation (OM 2); (3) change in health-related quality of life, measured using the EQ-5D-5L and EQ VAS for the period from enrollment to 24 months after allocation (OM 3); for OMs 1-3, changes within and between trial arms will be analyzed); and (4) health economic analyses comprising cost-effectiveness analyses based on OM 3 and cost-benefit analyses based on OMs 1 and 2 comparing the trial arms in terms of incremental costs based on direct and indirect costs related to the interventions throughout the intervention period (OM 4).

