Secondary OMs focus on health complaints, anxiety, and different aspects of work and work environment and comprise the following: change in physician-certified mean sickness absence rates (individual level) based on data from the Norwegian National Register of Sickness Absence (NAV sykefraværsregister) for the period 24 months before allocation compared with the period 12-24 months after allocation (OM 5); change in self-certified sickness absence rates (individual level; OM 6); change in psychosocial work environment, assessed using the Demand–Control–Support Questionnaire score (OM 7); change in social support from colleagues, assessed using the Nondirective and Directive Support Survey score (OM 8); change in job satisfaction, assessed using the Global Job Satisfaction score (OM 9); change in subjective health complaints, assessed using the subjective health complaints score (OM 10); change in health anxiety, assessed using the Whiteley index score (OM 11); and change in satisfaction with life, assessed using the Satisfaction With Life Scale score (OM 12).

OMs 6-12 are based on data from the trial questionnaires. Changes within and between trial arms will be analyzed for the following periods: enrollment to 12 months after allocation and enrollment to 24 months after allocation for each OM and 12 to 24 months when relevant.

For in-depth details regarding OMs, see ClinicalTrials.gov.

The trial questionnaire collects information on background variables (ie, type of employment, height, weight, education, income, smoking habits, alcohol consumption, and physical activity) as well as self-reported sickness absence and health care use. Several sections of the trial questionnaire are the same as those in the seventh and latest survey of the Tromsø Study (Tromsø 7), which took place in 2015-2016. For trial participants who also participated in Tromsø 7 and provided explicit consent, trial data will be linked to Tromsø 7 data to obtain an impression of natural intraindividual variation over time.

For all analyses, the possible impact of the COVID-19 pandemic will be addressed.

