## Discussion

### Preliminary Principal Findings

This trial will examine different aspects of workplace interventions and specifically compare the new interdisciplinary HIW program with usual monodisciplinary IWM in terms of health care use, health-related quality of life, and costs. As secondary objectives, it will also compare changes in individual sickness absence, psychosocial work environment, job and life satisfaction, health, and health anxiety at both the individual and group levels.

Although the number of finally enrolled workplaces was slightly below our desired target of 100 workplaces, individual participant numbers were well above the anticipated goal of 1000 enrolled participants. Despite computer-generated randomization, the distribution to the 2 intervention groups was slightly skewed toward the IWM group but not significantly different.

To date, the response rate for our questionnaire can be considered good, being 69.6% (962/1383), but response rates for questionnaires 2 and 3 will likely be lower. Incentives have proven to increase participation rate in follow-up questionnaires in randomized controlled trials [29]. We are already applying incentives in the form of gift certificates for 750 Norwegian kroners (US $84.31), which are randomly drawn from every 50 questionnaires received since the start of the study. Information about this was provided in the original email before questionnaire 1 and is included in emails for follow-up questionnaires 2 and 3.

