### Strengths and Limitations

Our trial is the first large-scale scientific evaluation of the *Health in work* program, which has thus far not been scientifically evaluated. The pragmatic design will reflect the effects that can be achieved by the 2 interventions in real life. The combined use of questionnaires and register data is a strength that could ameliorate the negative impact that a possible low response rate to follow-up questionnaires would have on representativeness.

A major strength is the trial design, with random allocation to one of the 2 intervention groups. As allocation was conducted by persons not involved in the production of allocation envelopes and only after individual consent forms were received, we have ameliorated the chances of selection bias (ie, the selective enrollment into the trial based on likelihood of the next treatment allocation). In addition, during the recruitment period, NWCs offered HIW only to workplaces participating in the trial (with a 50% chance of receiving HIW or IWM). IWM support was administered independent of trial participation. However, this could also have introduced a bias in that workplaces that wanted to receive HIW but were allocated to IWM will be less motivated for IWM activities or answering questionnaires. Attention will have to be given to possible differences in response rates of follow-up questionnaires in the HIW and IWM groups.

A potential limitation is that there might occur cross-contamination between trial arms, between nearby workplaces, and because of personnel serving both HIW and IWM interventions. In addition, generalizability could be influenced by regional workplace culture and characteristics, such as the experience of executing staff from NAV and specialist health care services.

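### Questionnaire outcomes rest on whoever answers, the only stated examination of non-response is of response rates, and no stated analysis uses the register data to examine or correct it

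*Protocol article*

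**What the plan says.** **Estimators.** Analysis of Data in the Protocol article says: "At the individual level, outcomes will be analyzed based on changes from enrollment". It lists two-sample tests and multilevel regressions. The paragraph before it assigns health-related quality of life to a difference-in-difference at the unit level. The same section says: "The analysis will be according to ITT regardless of protocol adherence".

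**Outcomes concerned.** Under Evaluation Outcomes, OM 3 (primary) is "change in health-related quality of life, measured using the EQ-5D-5L and EQ VAS for the period from enrollment to 24 months after allocation", and the cost-effectiveness part of OM 4 is based on it. For the secondary outcomes, "OMs 6-12 are based on data from the trial questionnaires", with contrasts for "enrollment to 12 months after allocation and enrollment to 24 months after allocation for each OM and 12 to 24 months when relevant".

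**Expected non-response.** Preliminary Principal Findings reports 962 of 1383 answers to questionnaire 1 and expects that "response rates for questionnaires 2 and 3 will likely be lower". Strengths and Limitations adds that workplaces that wanted HIW but were allocated to IWM may be less motivated to answer. Allocation is not blinded.

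**What is set against it.** Strengths and Limitations states: "Attention will have to be given to possible differences in response rates of follow-up questionnaires in the HIW and IWM groups". On the registers it says: "The combined use of questionnaires and register data is a strength that could ameliorate the negative impact" of a low follow-up response on representativeness. Two preventive measures are also described: gift certificates (Preliminary Principal Findings) and encouragement to keep answering after a workplace withdraws (Data Collection and Management).

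**Data at hand.** Data Collection and Management provides individual physician-certified absence and health care use from registers, from 24 months before to 24 months after allocation. Linkage has its own consent section.

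**The concern.** A change from enrollment to 24 months does not exist for someone who did not return questionnaire 3. The 0-12, 0-24 and 12-24 month changes can therefore come from three different sets of people. The unit-level difference-in-difference for OM 3 does not need paired answers, but each workplace value is still an average over that wave's respondents.

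If employees who are ill or often absent stop answering more in one arm than in the other, the arm contrast partly reflects who answered. The P value gives no sign of this. A comparison of response rates says how many are missing in each arm, not which people. So the article names an arm-related threat, pairs it with an examination that can miss it, and credits a data source that its stated analyses do not apply to it. A primary outcome and seven secondary outcomes are exposed.

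**Working it through.** **Figures in the article.** 962/1383 = 69.6%, as stated. The other 421 (30.4%) have no questionnaire 1 and so no change from enrollment. Questionnaire 1 was sent before allocation, so this gap concerns representativeness and precision. Arm-dependent bias comes from questionnaires 2 and 3. No follow-up response rate is given, so everything below is an assumption shown as a range.

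**Set-up.** No true effect. Let r be standardized register absence. In HIW, response is 60% whatever r is. In IWM, P(answer) = 1/(1 + exp(-(a - b·r))), with a = ln(0.6/0.4) = 0.405 and b = 0.4, 0.8 or 1.2. The correlation between enrollment and 24 months is taken as 0.6, so the change adjusted for enrollment has SD √(1 - 0.6²) = 0.8. Its correlation with r is ρ.

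**Formula.** Among IWM respondents the mean of r is E[r·p(r)]/E[p(r)] instead of 0. The spurious arm difference is |ρ| × 0.8 × |that mean|.

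| b | IWM response (HIW 60%) | mean r in IWM respondents | bias, ρ = -0.5 | bias, ρ = -0.2 |
|---|---|---|---|---|
| 0.4 | 59.6% | -0.156 | 0.06 SD | 0.02 SD |
| 0.8 | 58.8% | -0.290 | 0.12 SD | 0.05 SD |
| 1.2 | 57.8% | -0.395 | 0.16 SD | 0.06 SD |

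For example, at b = 1.2: 0.5 × 0.8 × 0.395 = 0.158. Simulated trials with 45 and 52 workplaces and 962 baseline respondents gave 0.06, 0.11 and 0.15-0.16 SD at ρ = -0.5. In every row the response rates differ by about two percentage points or less, so a rate comparison would give little warning.

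**Selection in both arms.** With b = 0.4 in one arm and 0.8 in the other, the bias is |ρ| × 0.8 × (0.290 - 0.156): 0.05 SD at ρ = -0.5 and 0.02 SD at -0.2. With equal b it is about zero.

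**Yardstick.** The individual-level planning difference is 5/17 = 0.29 SD, on an instrument that is not among the trial's outcomes. Against it, 0.06-0.16 SD is roughly 20-54% and 0.02-0.06 SD roughly 7-20%.

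**False positives.** At ρ = -0.5, two sets of simulated trials gave 12-14%, 28-35% and 46-58% for the three slopes, against 6-6.5% without selection. At ρ = -0.2, using the simulated standard error of about 0.073 SD, a bias of 0.02 SD gives about 6% and 0.06 SD about 13%.

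**What register data can recover.** Imputing by arm from earlier questionnaires and register absence left at most 0.004 SD. That follows from the set-up, in which response depends only on the variable used to impute and everyone is linked. If 70% are linked (assumed), 0.02-0.04 SD remains, about a third of the bias at ρ = -0.5.

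**The case against.** The strongest objection is scope. Missing-data methods usually sit in a statistical analysis plan, none is shown, and the article never says complete-case. That stands to this extent: the absence of a missing-data section is not a fault, and analysis restricted to respondents is inferred from the change score, not announced. What remains is what the article does state: the estimator, the threat, the examination set against it, and a strength claimed for the registers.

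The response-rate sentence is also a Discussion caveat. It does not say that equal rates will be taken as reassurance. That is fair, but it is the only examination named.

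Four stronger readings are tempting, and the documents do not support them.

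- **The register data go unused.** They supply OMs 2 and 5. What is absent is a stated analysis that applies them to questionnaire non-response.
- **The plan contradicts its own intention-to-treat promise.** The article defines that promise only against protocol adherence and makes no claim about missing questionnaires.
- **OM 3 needs paired individual answers.** It is assigned to a unit-level difference-in-difference, which may use each wave's respondents. It depends on respondents without necessarily being paired.
- **Nothing is done about non-response.** Incentives and encouragement are described. They are prevention, and they do not show or correct what is lost.

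The objection to the size also stands in part. The upper figures need selection in one arm only and a correlation of -0.5, neither of which the documents support. That correlation need not hold for job satisfaction, social support or health anxiety. Demotivation after an unwanted allocation, the mechanism the article itself names, need not show in absence registers.

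**Conclusion.** The point holds in a limited form. OMs 6-12 are analyzed as changes that only people answering both questionnaires can supply, and OM 3 rests on whoever answers each wave. The article expects lower and arm-related non-response, names only response-rate differences as something to examine, and states no analysis that uses register data to examine or correct questionnaire non-response.

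The size is unknown. Under absence-driven non-response in one arm at about 60% response, the spurious difference is about 0.06-0.16 SD at a correlation of -0.5 and 0.02-0.06 SD at -0.2. It is about zero if selection is equal in both arms. These are conditional illustrations, not estimates for this trial. A reader might infer that the questionnaire results will be badly biased, or that register data would remove the bias; the documents support neither. A change is still worthwhile because a primary outcome is exposed to a threat the article itself names, and the data to examine it are already being collected.

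**What to change.** For OM 3 and OMs 6-12:

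1. Fit one repeated-measures multilevel model to all available questionnaires, with workplace and person effects, in place of separate change scores. The 12- and 24-month arm contrasts come from the arm-by-time terms.
2. Alongside response rates, compare register absence and health care use of responders and non-responders by arm.
3. For participants who consented to linkage, add an analysis that imputes missing follow-ups separately by arm from earlier questionnaires and register data before and after allocation. Report it beside the responder analysis.

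The cost is some analysis work, since linkage is already planned. Three limits should be stated. Participants without linkage consent get no help from the registers. The individual register absence is physician-certified only. Non-response driven by the unobserved score itself is not removed. Links to later questionnaires go to the email address given in questionnaire 1, so the model gains mainly from people who missed one follow-up, not from the 421 who did not answer questionnaire 1.

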**Methods:**

Data will be collected from national registers, trial-specific registrations, and questionnaires. Effects will be explored using difference-in-difference analysis and regression modeling. Multilevel analysis will visualize any cluster effects using intraclass correlation coefficients.

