## Methods

### Trial Design and Setting

This protocol presents a pragmatic, cluster-randomized, multicenter superiority trial with 2 parallel arms and a 1:1 allocation ratio. HIW and IWM interventions are to be carried out at workplaces throughout the county of Troms and Finnmark, Norway’s northernmost county, which covers an area of approximately 750,000 km^2^ and has a population of approximately 243,000 people. Workplaces in both urban and rural areas are included.

As both IWM and HIW interventions are aimed at all employees within a workplace, randomization must be conducted at the workplace level rather than at the level of individual employees.

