### Statistical Analysis

#### Power Calculation

The calculation of the sample size for the number of workplaces is pragmatic and based on Odeen et al [8]. ITT sickness absence will be collected at the unit level, and a 10% reduction from 6.6% (mean certified sickness absence in Troms) to 5.9% (SD 2.5%) will be considered significant in both a clinical and societal context. Odeen et al [8] demonstrated a statistically significant 11% difference in rate ratios at the unit level, with 42 and 48 units in the 2 arms. We consider actual units for inclusion as comparable and, therefore, plan to include 50 workplaces in each arm in line with the study by Johnsen [23] on workplace interventions in kindergartens.

At the individual level, the necessary sample size to detect a clinically significant difference within the arms was calculated according to the hypothetical use of the patient activation measure. A clinically significant difference in patient activation measure between the arms can be set at *D*=5 [27]. On the basis of this, and using a quantitative method where *f*(*a*=0.05, *b*=0.20)=10.5, we can calculate the necessary sample size for the trial arms: 182 (*n* = 2[*SD*/*D*]^2^ × *f*[*a*,*b*]) individuals in each arm if the SD is 17, strength (*b*) is 80%, and significance level (*a*) is 5%. Therefore, we need to include a total of 364 participants in the trial. To take into account the lack of independence between workers in clusters, this number should be corrected by *the variance inflation factor* 1 + (*n* − 1)*ρ*, where *n* is the average cluster size and *ρ* is the intracluster correlation coefficient for the particular outcome [28]. With the value of *n* being 4, the inflation factor equals 1.3 when *P* equals .10; thus, each trial arm should include 240 individuals. This indicates that, with a 50% response rate and a mean workplace size of 20 employees, we will have the power to perform gender-stratified analyses with 50 workplaces in each study arm.

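### The analysis section names both cluster-ignoring tests and multilevel models for individual-level outcomes and does not say which one governs the between-arm comparison

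*Protocol article*

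**What the plan says.** The Trial Design and Setting section explains that "randomization must be conducted at the workplace level rather than at the level of individual employees". The Power Calculation section recognizes what follows for individual outcomes: "To take into account the lack of independence between workers in clusters, this number should be corrected by" a variance inflation factor, evaluated there with an ICC of 0.10.

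The paragraph on individual outcomes under Analysis of Data begins: "At the individual level, outcomes will be analyzed based on changes from enrollment". The next sentence says that "2-tailed *t* tests or Mann-Whitney *U* tests and chi-square tests will be used when appropriate". Two model-based analyses follow in the same paragraph:
- for sick leave, "A generalized linear mixed effects Poisson model will be used to investigate possible differences in percentage of sick leave between the 2 trial arms";
- for other outcomes, according to type, "A multivariable, multilevel logistic, ordered logistic, and linear regression allowing for clustering at the unit level will be used".

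The preceding paragraph places difference-in-difference analyses of sickness absence, health care refunds and health-related quality of life at the workplace level. The abstract adds that "Multilevel analysis will visualize any cluster effects using intraclass correlation coefficients". One significance rule covers everything: "We will use 2-sided *P* values with *α*<.05 level of significance for all tests".

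**The concern.** Two-sample t, Mann-Whitney U and chi-square tests treat each worker as an independent observation. When whole workplaces are allocated and coworkers resemble each other, the between-arm difference varies more than these tests assume. Standard errors are then too small, confidence intervals too narrow and P values too low. The protocol corrects its sample size for this and then lists tests that do not.

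The limiting words at the end of the sentence on simple tests are not defined. They may mean choosing among the three tests by data type, or choosing between simple tests and models. For an outcome such as the work environment score or support from colleagues, the text permits both an unadjusted test and a multilevel regression. The two can disagree, and nothing says which result counts. With six such questionnaire outcomes (OM 7 to OM 12), each analyzed over two or three periods, the opening for conflicting or selectively favourable results is real.

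**Working it through.** **Inputs**
- Significance level: two-sided 5%, all tests (Analysis of Data).
- Planning ICC 0.10, cluster size 4, inflation factor 1.3, 182 per arm raised to 240 (Power Calculation).
- Planned respondents per workplace: 20 employees × 50% response = 10 (Power Calculation).
- Actual respondents per workplace at enrollment: 962/97 = 9.9 (Results).
- Allocation: 45 and 52 workplaces (Results).
- Assumptions of this check: ICCs of 0.01, 0.02 and 0.05; about 5 respondents per workplace at follow-up.

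**The plan's own figure.** For a difference of 5, SD 17, 80% power and two-sided 5%, n = 2 × (17/5)² × 7.85 = 181.5, so 182 per arm. The inflation factor is 1 + (4 − 1) × 0.10 = 1.3, and 182 × 1.3 = 236.6, close to the stated 240. The protocol therefore does apply a clustering correction. (The multiplier printed there, 10.5, gives 242.8 rather than 182. That is a separate matter and does not affect this check.)

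**Effect of ignoring clustering.** With m respondents per workplace and ICC ρ, the design effect is DE = 1 + (m − 1)ρ. The true standard error is √DE times the one a simple test uses, so the true type I error is 2 × P(Z > 1.96/√DE).

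| m per workplace | ICC | DE | True type I error |
|---|---|---|---|
| 4 (power section) | 0.10 | 1.30 | 8.6% |
| 9.9 (962/97) | 0.10 | 1.89 | 15.4% |
| 10 (20 × 50%) | 0.10 | 1.90 | 15.5% |
| 5 (assumed) | 0.10 | 1.40 | about 10% |
| 10 | 0.05 (assumed) | 1.45 | 10.4% |
| 10 | 0.02 (assumed) | 1.18 | 7.1% |
| 10 | 0.01 (assumed) | 1.09 | 6.1% |

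For 9.9 respondents: DE = 1 + 8.92 × 0.10 = 1.892, √1.892 = 1.38, and 1.96/1.38 is about 1.42, which gives 15.4%. For 5 respondents: DE = 1 + 4 × 0.10 = 1.40, and 1.96/√1.40 = 1.66, which gives about 10%.

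**Simulation.** With 45 and 52 equal-sized workplaces, no true effect and 4000 runs, the unadjusted t test rejected in 15.2% (m = 10, ICC 0.10), 10.4% (m = 10, ICC 0.05), 6.6% (m = 10, ICC 0.02) and 9.9% (m = 4, ICC 0.10). A t test on workplace means in the same runs rejected in 4.5% to 5.9%. The 5.9% belongs to the m = 4 run, so part of that run's gap from the formula's 8.6% may be simulation noise.

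**Which outcomes are exposed.**
- OM 3 (quality of life) also has a workplace-level difference-in-difference analysis.
- OM 5 and OM 6 (individual sickness absence) fall under the mixed Poisson model.
- OM 7 to OM 12 have multilevel regression and the simple tests side by side, with no order between them.

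**The case against.** The strongest reply is that the paragraph already deals with clustering. The sentence on simple tests is qualified, the sentences after it name mixed and multilevel models, and the abstract mentions only multilevel analysis. This stands against a stronger reading that a reader might infer, namely that the trial will compare its individual outcomes by cluster-ignoring tests and that all its P values will be too low. The document does not say that, and no primary outcome is shown to depend on such a test.

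A second reply is that the simple tests may be meant for baseline description, within-arm change or workplace means. The text does not fit these readings well. The sentence directly follows the one on change since enrollment, the paragraph is explicitly about individuals, Mann-Whitney U compares independent groups rather than paired values, and the 5% level is applied to every test. Still, the sentence names no comparison, so its between-arm role is inferred.

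Third, the 15% figure is not a forecast. The 9.9 counts questionnaire 1 respondents, a change score also needs a follow-up answer, and the protocol expects lower response later. The ICC of 0.10 was chosen for a hypothetical instrument that is not a trial outcome. Both points stand and are the reason for giving a range. In the other direction, unequal workplace sizes generally raise the design effect, and OM 7 and OM 8 describe conditions that coworkers share, so a negligible ICC cannot be presumed.

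A reader might also take 1383/97 = 14.3 per workplace for register outcomes, which at ICC 0.10 gives about 20%. The documents do not support this: register linkage has its own consent section, no linkage count is given, and the individual register outcome (OM 5) is sick leave, which has the mixed Poisson model.

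**Conclusion.** The point holds as an unresolved choice between valid and invalid analyses of the same outcomes. The invalid option is named in the text, so this is more than detail left to an analysis plan. The consequence is conditional: it arises only if the simple tests are applied to individuals between arms. The nominal 5% would then be about 15% at enrollment response and the protocol's own planning ICC, about 10% with roughly 5 respondents per workplace at that ICC, and about 6% to 10% at 10 per workplace for ICCs of 0.01 to 0.05. None of the scenarios computed keeps 5%. The figures assume equal workplace sizes. The protocol gives no ICC for any actual trial outcome, so the true inflation is unknown within and around this range.

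**What to change.** In Analysis of Data, state that between-arm inference on all individual-level outcomes rests on the multilevel or mixed models already named, with a workplace random effect. State also that t, Mann-Whitney U and chi-square tests are used only for description or on workplace-level summaries, that is, on the 97 workplace means where a simple or rank test is wanted. Settle this before any between-arm result is produced.

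The cost is wording only, with no new data, design change or method. P values will be somewhat less favourable than the unadjusted tests would give.

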### Specific Objectives

The main objective of this trial is to compare the effects of monodisciplinary IWM (treatment as usual) and interdisciplinary HIW interventions in terms of changes in overall sickness absence, health care use, health-related quality of life, and costs. The secondary objectives are to compare changes in individual sickness absence, psychosocial work environment, job and life satisfaction, health, and health anxiety at both the individual and group levels. Comparisons will be conducted both within and between trial arms.

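### Several primary outcomes are each tested at an unadjusted two-sided .05 with no hierarchy or success rule, so the chance of a false primary claim is about 14-26% for 3-6 independent between-arm tests

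*Protocol article*

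**What the plan says.** The Protocol article, under Trial Design and Setting, describes a two-arm superiority trial. Under Evaluation Outcomes it argues that the program's aims are not ranked and concludes that "it is impossible to define a single primary OM for this trial and, thus, the four primary OMs are as follows". The four are:

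- OM 1: "change in overall sickness absence rates (self- and physician-certified) at the workplace (unit level) in percentage of planned workdays".
- OM 2, on the use of health services: "assessed using data from the National Register of Control and Health Service Refunds (The Norwegian Directorate of Health) and the Norwegian Patient Register".
- OM 3, the quality-of-life outcome: "measured using the EQ-5D-5L and EQ VAS for the period from enrollment to 24 months after allocation (OM 3").
- OM 4, the economic outcome: "health economic analyses comprising cost-effectiveness analyses based on OM 3 and cost-benefit analyses based on OMs 1 and 2 comparing the trial arms".

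The same section adds that "for OMs 1-3, changes within and between trial arms will be analyzed". Specific Objectives says more generally: "Comparisons will be conducted both within and between trial arms".

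Under Analysis of Data, difference-in-difference methods are assigned to sickness absence, health care refunds and quality of life. The error rule that closes the testing plan is "We will use 2-sided *P* values with *α*<.05 level of significance for all tests". The article gives no order among the primary outcomes, no requirement that all of them succeed, and no adjustment of the level.

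**The concern.** A level of .05 per test controls the error of one test. With several primary outcomes and no rule linking them, nothing in the text stops one result below .05 from being read as showing that *Health in work* is superior. The error rate of that reading rises with the number of tests. A decision on a resource-demanding program could then rest on a primary finding whose real false-positive risk is two to five times the nominal 5%.

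The within-arm analyses are a lesser concern of a different kind. A change from before to after in one arm is not a randomized comparison, and a significant change in one arm beside a non-significant change in the other is not a test of the difference between them.

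**Working it through.** **Inputs from the Protocol article.** The level is .05, two-sided, for all tests (Analysis of Data). There are four primary outcomes, and OM 3 has two named measures (Evaluation Outcomes). OM 2 draws on two registers, and the text does not say whether this means one test or two. OM 4 holds two kinds of economic analysis, and the text does not say whether either yields a P value.

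**Inputs assumed.** The correlation between the primary tests is not given, so a range of 0 to 0.7 is used. It is also assumed that any one significant between-arm primary result may support a claim.

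**Starting point.** The only error figure in the plan is .05 per test. The formula 1 − (1 − 0.05)^m returns .05 at m = 1. The plan states no family error rate to reproduce.

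**Number of between-arm primary tests, m:**

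- m = 3: OM 1, OM 2 and one OM 3 measure, with OM 4 estimated only.
- m = 4: as above, with EQ-5D-5L and EQ VAS both tested.
- m = 5: as m = 4, plus one OM 4 test or a second OM 2 test.
- m = 6: as m = 4, plus two further tests from OM 2 and OM 4.

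**Independent tests:**

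- 1 − 0.95^3 = 14.3%
- 1 − 0.95^4 = 18.5%
- 1 − 0.95^5 = 22.6%
- 1 − 0.95^6 = 26.5%

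**Correlated tests.** These come from simulating m equally correlated two-sided z-tests with no true effect, one million replicates each:

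| m | correlation 0.3 | 0.5 | 0.7 |
|---|---|---|---|
| 3 | 13.6% | 12.5% | 10.9% |
| 4 | 17.4% | 15.7% | 13.0% |
| 5 | 20.9% | 18.2% | 14.8% |
| 6 | 24.2% | 20.7% | 16.4% |

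Even the most favorable cell, 10.9%, is more than twice 5%.

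**Within-arm changes and the calendar.** For OMs 1 and 2 the comparison is 24 months before allocation against months 12-24 after it. Inclusion ran from June 2019 to July 2021 (Results), and the trial was halted from mid-March to September 2020 (Timeline). On the nominal schedule, a workplace allocated in June 2019 has a before-period of June 2017 to June 2019 and an after-period of June 2020 to June 2021. One allocated in July 2021 has a before-period of July 2019 to July 2021 and an after-period of July 2022 to July 2023. The 2020 disruption thus falls in the after-period for early workplaces and in the before-period for late ones. A within-arm change mixes this with any effect. The between-arm contrast has a concurrent control arm and the within-arm change has none.

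**The case against.** The strongest reply is that outcomes which address separate aims may each be reported on their own at .05. The protocol gives a reason for having several, and success rules are often left to an analysis plan, which is not shown here. Silence would indeed be excusable in a condensed article. But the article is not silent: it fixes one level for all tests, and that covers the primary family. Reporting each outcome separately is defensible if declared, provided that no single result is then taken as overall superiority. The article declares neither this nor an all-must-succeed rule, which would need no adjustment.

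Three further objections stand and limit the point.

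- Only OM 3 clearly has two measures. The two registers in OM 2 may feed one total, and OM 4 may never be tested by P value. The family size is therefore a range.
- Independence is doubtful. EQ-5D-5L and EQ VAS come from the same respondents, and OM 4 is built from OMs 1-3. Hence the correlated figures.
- The article nowhere says that one significant result suffices, or that within-arm change is evidence of efficacy. It assigns difference-in-difference, a between-arm method, to the main outcomes and promises to address the pandemic in all analyses.

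Two stronger readings are tempting. A reader might infer that all four primary outcomes are tested within arms. The specific sentence covers OMs 1-3 only, OM 4 is described as comparing the arms, and the sentence in Specific Objectives is general. A reader might also count three tests for each of five measures and treat all fifteen as independent. They are not, because each between-arm contrast is the difference of the two within-arm changes. Nor is a chance within-arm result by itself a false claim of superiority, so such a count does not measure the error at issue.

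**Conclusion.** The point holds for the between-arm primary family. With .05 for every test and no hierarchy or success rule, the chance of at least one false primary claim is about 14-26% for 3-6 independent tests, and about 11-16% if the tests are correlated at 0.7. This assumes no true effect on any of the outcomes tested, and that any one significant result may support the claim. The exact figure depends on a test count and a correlation that the article does not give, so the range should be quoted and not a single value.

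The within-arm point is secondary. These analyses may be reported, but for OMs 1-3 they cannot support a claim of effect.

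**What to change.** Replace the .05-for-all-tests rule with a declared confirmatory family: the between-arm difference-in-difference contrasts of OM 1, OM 2 and OM 3, one pre-named measure each, tested with Holm's procedure at a family level of .05. Which OM 3 measure to use, and how the two registers form one OM 2 measure, is for the sponsor to choose before the outcome data are examined. Treat the other OM 3 measure as secondary and report OM 4 by estimation. Present within-arm changes descriptively with confidence intervals and make no claim of effect from them.

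The change is one of wording, subject to the approval and registration route that the article sets for substantial modifications. No participant had received questionnaire 3 by February 20, 2022, so as of the article it could still precede the 24-month questionnaire results.

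The cost is power. The Holm thresholds are .05/3 = .0167, then .025, then .05. As an illustration, a contrast with 80% power at .05 has an expected z of 1.960 + 0.842 = 2.802. Against the first-step critical value of 2.394, its power is Φ(2.802 − 2.394) = Φ(0.408), about 66%. This is the worst case for one outcome, because the threshold relaxes once another outcome is rejected.
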